##### Monitoring in the home environment

Caregivers receive a push notification at pre-specified times (2, 6, 12, 24, 48 h after discharge), requesting them to assess their child’s health status. Included items are general condition (alertness, behavior for children up to 3 years old, or orientation for children 3 years and older), pupillomotor function, motoric function, eating/drinking behavior for children up to 3 years old or headaches for children 3 years and older, and nausea/vomiting. The assessment is age-adapted and uses binary answers that are structured so that critical responses can be easily identified. Caregivers are instructed to contact the treating ED if they have answered any item with a critical response. The app will not interact with parent’s responses and does not have a built-in alarm function. All recommendations by the app will be displayed statically already before responses have been entered. Each inquiry will remain open to answer until the next scheduled inquiry.

#### Definition of outcomes

The primary outcome consists of two co-primary outcomes (CPO) to assess the effectiveness of the intervention in reducing hospital admissions and the safety of the nCP in terms of unplanned re-visits. Secondary outcomes comprise clinical safety outcomes, healthcare economic evaluation, and aspects of health service delivery.

##### Primary outcomes

 1st Co-primary outcome: Relative risk of hospitalization among all included cases (outpatient and inpatient) at initial ED presentation.

2nd Co-primary outcome: Proportion of cases with unplanned re-visit within 72 h after discharge from the ED.

##### Secondary outcomes

Secondary hospitalization following initial outpatient management, re-visits (all-cause and TBI-related), missed clinically relevant intracranial injury, admission to intensive care unit, neurosurgical intervention, death, costs/cost-effectiveness, acceptance, and barriers to implementation.

#### Sample size calculation

The sample size calculation considered both CPOs, using generalized linear mixed models (GLMM) for both analyses. To estimate the relative risk of hospitalization, a GLMM with log link is planned. The calculation is based on hospitalization data from 2022 (ICD-10 German modification S02.- and S06.-) from 14 study sites that provided ED data on ambulatory care and hospitalizations during the pre-planning of the study with a mean admission rate of 61% (range [22%, 93%]). For the sample size calculation, a mean hospitalization rate of 50% was assumed to account for possible changes in hospitalization behavior due to implementation training or fluctuating admission capacities. The study’s aim is a relative risk reduction of 20% (relative risk = 0.8). The GLMM also requires the intra-cluster correlation coefficient (ICC), which is estimated at 0.142 based on available data (Fleiss-Cuzick estimator) and set at 0.15 for the calculation. With a power of 0.9, *α* = 0.05, and 11 study sites a sample size of 1056 patients is required for the first CPO.

The second CPO is examined using a non-inferiority test. A GLMM with identity link will be applied to estimate the risk difference. Based on an unplanned re-visit rate of 6% in one of the participating study sites and literature-reported rates of 1.5% [11], an average unplanned re-visit rate of 3% is assumed before the intervention. A 2-percentage point increase in unplanned re-visits during the intervention is anticipated due to potentially increased parental need for reassurance. In addition, a 5-percentage point increase in unplanned re-visits is considered medically acceptable, as patients would otherwise still be in hospital, and spot-ED presentations are considered less burdensome than hospitalization. Thus, an unplanned re-visit rate in the nCP that ≤ 7 percentage points above standard care is considered non-inferior. With an assumed ICC of 0.1, power of 0.9, *α* = 0.025, and 11 participating study sites, a sample size of 1320 (10 per study site per month) is needed. Due to the very short observation period, a drop-out rate of 5% is assumed, resulting in a required sample size of 1390 (11 per study site per month).

The leading sample size is derived from the non-inferiority testing plus the assumed dropout rate is established as the recruitment target for the prospective clinical study.

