#### Statistical methods

##### Clinical evaluation

For the hospitalized patient group, the relative risk change due to the nCP for the binary endpoint “hospitalization” will be estimated using a GLMM with log link and modeling fixed effects for intervention and time as well as random study site effects. A Wald Z-test will be used to test the null hypothesis of equal hospitalization risk with and without the intervention at a significance level of *α* = 0.05. For the non-inferiority analysis with respect to the proportion of patients with unplanned re-visits, the absolute risk difference will be considered. A GLMM with an identity link for the binary endpoint of unplanned re-visits, again with fixed effects for intervention and time and random study site effects, will be applied. A one-sided 97.5% confidence interval will be estimated for the difference in unplanned re-hospitalization rates. If the non-inferiority margin is not overlapped by the confidence interval, the null hypothesis of inferiority will be rejected. The two endpoints will be tested co-primary, i.e., both statistical tests have to be significant for a study success. As co-primary testing does not inflate the type I error rate, there is no need to correct for multiple testing, while an overall power of more than 80% can be preserved assuming that the two tests are independent each with a power of 90% (power of 1 st COP times power of 2nd COP).

Secondary outcomes will be analyzed using appropriate statistical methods as specified in the statistical analysis plan (SAP) prior to the beginning of the study. Clinical documentation will be performed in the software tools designed for the SaVeBRAIN.Kids study to ensure high data quality.

Primary analyses will be conducted as intention to treat, comparing outcomes in patients recruited before and after the study sites’ staff introduction to the nCP according to the randomization. Study sites with major protocol violations (e.g., late or no training for the nCP) will be excluded from a sensitivity analysis of a per-protocol study population. Further details will be specified in the SAP.

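### With time effects in the model, as planned, the first co-primary has about 55% power at 1056 patients and 64% at 1320, not 90%; overall power is about 53%, not more than 80%

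*Protocol article*

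**What the plan says.** All references are to the protocol article.

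- **Sample size calculation, first co-primary (hospitalization).** "a mean hospitalization rate of 50% was assumed", the target relative risk is 0.8, and the ICC is estimated at 0.142 and "set at 0.15 for the calculation". With power 0.9, α = 0.05 and "11 study sites a sample size of 1056 patients is required for the first CPO".
- **Sample size calculation, second co-primary (unplanned re-visits).** The control rate is 3%, a rise of 2 points is anticipated, the margin is 7 points, the ICC is 0.1, α is 0.025 and power is 0.9; "a sample size of 1320 (10 per study site per month) is needed". This becomes the leading size, raised to 1390 for 5% drop-out.
- **Interventions.** There are 11 sites over 12 months. All start in control and one site switches each month.
- **Clinical evaluation.** The hospitalization model is a log-link GLMM, "modeling fixed effects for intervention and time as well as random study site effects". Equality of the two risks is the null, tested by a Wald Z statistic at α = 0.05. The re-visit model has the same fixed and random effects with an identity link. Both tests must be significant, and "an overall power of more than 80% can be preserved" because each is taken to have 90% power and to be independent of the other.

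**The concern.** In this design the share of sites under the intervention rises from 0 of 11 in month 1 to 11 of 11 in month 12, so intervention and calendar time are strongly confounded. Adjusting for time, which the plan rightly does, costs much of the information. The stated size for the first co-primary looks too small to have paid that cost.

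Success requires both tests. If the first has far less than 90% power, the second co-primary is not the one that determines the sample size, and the overall power claim fails. A true 20% relative reduction in admissions, the effect the trial aims for, would then often not be declared. The protocol implies a risk of failure below 20%.

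**Working it through.** **Design constants.** Sites I = 11 and periods T = 12. The sites have 11, 10, …, 1 intervention months, so U = 66. The sums of squared column totals and row totals are W = V = 506. There are 132 site-months: 1056 is 8 per site-month, 1320 is 10, and 1390 is 10.53.

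**Variance with fixed monthly effects and a random site intercept (Hussey–Hughes).** With s² the variance of a site-month mean and τ² the between-site variance:

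Var = I·s²·(s² + T·τ²) / [(I·U − W)·s² + (U² + I·T·U − T·W − I·V)·τ²]

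- I·U − W = 726 − 506 = 220
- U² + I·T·U − T·W − I·V = 4356 + 8712 − 6072 − 5566 = 1430
- Hence Var = 11·s²·(s² + 12τ²) / (220·s² + 1430·τ²)

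**First co-primary, inputs.** The rates are 0.50 and 0.50 × 0.8 = 0.40. Mean binomial variance is (0.25 + 0.24)/2 = 0.245. With ICC 0.15, τ² = 0.15 × 0.245 = 0.03675 and s² = 0.85 × 0.245/n = 0.20825/n. Power = Φ(0.10/SE − 1.96).

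**Trying to reproduce 1056 at 0.9**

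- Time effects omitted, two-sided: SE 0.0327 and power 0.86 at 8 per site-month; 0.93 at 10. About 1214 patients would be needed for 0.9.
- Time effects omitted and a further relaxation: one-sided α = 0.05 gives 0.92 at 8 per site-month (0.89 at 7), and ICC = 0 gives 0.91 at 8. Either would lead to 8 per site-month.
- Time effects included: no variant tried comes near 0.9 at 1056.

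**Result under the stated model**

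| Patients per site-month | Total | SE | Power |
|---|---|---|---|
| 8 | 1056 | 0.0479 | 0.55 |
| 10 | 1320 | 0.0430 | 0.64 |
| 10.53 | 1390 | 0.0420 | 0.66 |
| 20 | 2640 | 0.0307 | 0.90 |

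For n = 8: s² = 0.02603, so Var = 0.13373/58.279 = 0.002295 and SE = 0.0479. Then 0.10/0.0479 − 1.96 = 0.13 and Φ(0.13) = 0.55. At 1320, 0.9 is reached only for a relative risk of about 0.72.

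**Sensitivity, time effects included (1056 / 1320)**

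- Linear time instead of monthly indicators: 0.55 / 0.64. Quarterly time: 0.55–0.58 / 0.63–0.67.
- ICC 0.05–0.30: 0.54–0.62 / 0.63–0.72. ICC 0: 0.72 / 0.82.
- One-sided α = 0.05: 0.65–0.67 / 0.72–0.75.
- Marginal log-link information: 0.52 / 0.61, needing 24 per site-month (3168) for 0.9.
- Control rate at the observed 61%: 0.72 / 0.81.
- Simulation with varying site rates: linear mixed model 0.56 / 0.65, log-binomial model 0.57 / 0.65.

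**Second co-primary.** The distance to the margin is 0.07 − 0.02 = 0.05, and the ICC is 0.1.

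- Variance at 3% in both phases, time effects included: 0.88 at 9 per site-month and 0.91 at 10. This reproduces the stated 1320. Without time effects, power at 10 would be above 0.99.
- Variance at the planned 3% and 5%: mean (0.0291 + 0.0475)/2 = 0.0383, SE 0.0173, power Φ(0.05/0.0173 − 1.96) = 0.82. A marginal calculation gives 0.80.

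**Overall power, taking independence as the plan does**

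- At 1320: 0.64 × 0.82 = 0.53.
- At 1320, second co-primary at 0.91: 0.64 × 0.91 = 0.58.
- First co-primary at all 1390, second at 0.91: 0.66 × 0.91 = 0.60.
- Stated: 0.9 × 0.9 = 0.81.

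**The case against.** Five points can fairly be made for the plan.

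- **The origin of 1056 is unknown.** Leaving out time effects gives 0.86, not 0.90, so that alone does not explain the figure. This stands. The review can say that 1056 does not follow from the stated model, but not how it arose.
- **Two-sided testing is an inference.** The text gives only α = 0.05. A null of equal risk reads as two-sided, and a one-sided test still gives at most 0.75 at 1320.
- **The second co-primary is a question of convention.** Its 1320 is reproduced with time effects if the 3% variance is used throughout. This stands in part: 0.82 follows from the plan's own anticipated 5%, but a range of 0.80 to 0.91 is fair. It also suggests that the two sizes rest on different models, although the same fixed and random effects are prescribed for both.
- **The 53% is one point in a range.** Hospitalization is known at first presentation, so nearly all 1390 may contribute to that outcome. With this and the kinder convention, overall power reaches about 0.60, still far below 0.80.
- **The 50% control rate is deliberately cautious.** At the observed mean of 61% the first co-primary would have about 0.81 at 1320 (0.84 in a log-link variant). The practical shortfall could therefore be smaller, but the claim was made at 50%, and 0.9 is not reached at 61% either.

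**Conclusion.** The concern holds. Under the inputs, design and model that the article itself fixes, the first co-primary has power of about 0.55 at 1056, 0.64 at 1320 and 0.66 at 1390, against a stated 0.9. Overall power is about 0.53 at 1320 when the second co-primary is computed with both planned rates, and at most about 0.60 on the most generous reading of the second co-primary and of the evaluable number. A true relative risk of 0.8 would miss trial success roughly 40 to 47% of the time. The first co-primary, not the second, is the one that determines the sample size.

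This rests on equal numbers per site-month, a constant intervention effect, no decay of within-site correlation, a normal-approximation Wald test and independence of the two tests. Correlation decay or a small-sample correction for 11 clusters would generally lower power further. This cannot be left to the SAP, because the article states the sample size, the model and the power claim.

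**What to change.** Recompute both sample sizes under the model in the Clinical evaluation section, and state the variance convention, the sidedness of the first test and how time is coded. Then:

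- remove the statement that 1056 patients suffice for the first co-primary at 0.9;
- remove the overall power claim of more than 80%;
- report, at 1320 evaluable patients, power of about 0.64 for a relative risk of 0.8 (0.90 for about 0.72) on the first co-primary, about 0.82 on the second (0.91 only if the 3% variance is used in both phases), and about 0.53 overall, with the sensitivity range;
- correct the statement that the non-inferiority test gives the leading sample size.

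The cost is restated figures in the protocol and SAP and a less favourable power statement; the design need not change. Restoring 0.9 on the first co-primary would be a separate decision. It needs about 20 patients per site per month, above the maximum of 13 in the Recruitment section, or additional sites, which that section already allows for if recruitment falters. Pre-specified baseline covariates might recover some power, but that gain has not been calculated and is not part of the correction.

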**Methods:**

The SaVeBRAIN.Kids trial will implement and test a novel care pathway (nCP) for evidence-based standardized risk assessment, structured observation in the emergency department (ED) for several hours, and technology-supported home monitoring with the aim to reduce hospitalizations. This non-inferiority multicenter study will be carried out using a cluster-randomized stepped-wedge design, with all centers starting in the control phase and sequentially transitioning to the intervention. Eligible participants (age ≥ 3 months and < 18 years) must present within 48 h of head injury, have minimal symptoms (Glasgow coma scale ≥ 14), and no risk factors for intracranial complications. The co-primary outcomes are the relative risk of hospitalization and the proportion of unplanned re-visits within 72 h of presentation to the ED for ambulatory cases. Secondary outcomes include clinical safety measures, cost-effectiveness, and process evaluation. Based on power calculations (*α* = 0.05, power = 0.9), 1390 patients will be recruited over 12 months.

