#### Interventions

The trial is carried out using a cluster-randomized stepped wedge design. The 11 study sites will participate in the study over 12 months. All study sites will start in the control phase and one study site (cluster) per month will switch to the intervention arm, which will be carried out until the end of the study. The switching order will be randomized, and study centers will be informed 8 weeks in advance to switching.

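### The 90% power claimed for hospitalization at 1056 patients does not hold under the planned model with a time effect: it is about 54–64%, and 63–73% at 1320, so overall power above 80% is out of reach

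*Protocol article*

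**What the plan says.** All places are in the protocol article.

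- **Design (Interventions).** "The 11 study sites will participate in the study over 12 months". Further: "All study sites will start in the control phase and one study site (cluster) per month will switch to the intervention arm".
- **First co-primary, size (Sample size calculation).** For planning, "a mean hospitalization rate of 50% was assumed", with a target relative risk of 0.8, an ICC of 0.15, power 0.9 and alpha 0.05. The result: "11 study sites a sample size of 1056 patients is required for the first CPO". No time effect is mentioned in this calculation.
- **First co-primary, analysis (Clinical evaluation).** A log-link GLMM "modeling fixed effects for intervention and time as well as random study site effects", tested with a Wald Z-test of equal risk.
- **Second co-primary.** 1320 patients (10 per site per month), raised to 1390 for 5% dropout. The section concludes: "The leading sample size is derived from the non-inferiority testing".
- **Overall power (Clinical evaluation).** Both tests must succeed, and "an overall power of more than 80% can be preserved assuming that the two tests are independent each with a power of 90"%. The Abstract repeats power 0.9 and states that "1390 patients will be recruited over 12 months".

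**The concern.** In a stepped wedge the share of sites under intervention rises with calendar time, so intervention and time are strongly collinear. Adjusting for time is right, because it protects against secular trends, but it costs precision. A sample size that ignores this cost will be too small for the model that is actually fitted.

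The effectiveness test would then miss the planned 20% relative reduction about one time in three at the planned enrolment. A non-significant result could be read as an ineffective pathway, because the trial is presented as having 90% power per endpoint and more than 80% overall.

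**Working it through.** **Inputs.** I = 11 sites, T = 12 months and 132 site-months, of which 66 are under intervention (Interventions). Control rate 0.50, relative risk 0.8 (risk difference −0.10, log RR −0.223), ICC 0.15, two-sided 5% (Sample size calculation; Clinical evaluation). 1056/132 = 8 per site-month, 1320/132 = 10, and 1390/132 = 10.53.

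**Formula.** Hussey–Hughes generalized least squares variance with a random site effect and a fixed time effect. With U = 66 and W = V = 506:

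var = I·s²(s² + T·t²) / [(IU − W)s² + (U² + ITU − TW − IV)t²] = 11·s²(s² + 12t²) / (220s² + 1430t²)

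where s² = (1 − ICC)·p(1 − p)/n and t² = ICC·p(1 − p). Power = Φ(|effect|/SE − 1.96). The risk-difference scale uses SE directly; the log scale uses SE/0.5.

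**Step 1: reproduce 1056.** With the time effect left out, on the log scale:

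| n per site-month | total | SE (log RR) | power |
|---|---|---|---|
| 7 | 924 | 0.0705 | 88.6% |
| 8 | 1056 | 0.0661 | 92.2% |

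Eight is the smallest whole number reaching 90%, and 8 × 132 = 1056, the printed figure.

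**Step 2: add the planned time effect.** For n = 8, s² = 0.85 × 0.25/8 = 0.02656 and t² = 0.15 × 0.25 = 0.0375. The variance is 0.002341, against 0.001091 without time, a ratio of 2.15. SE = 0.0484 (risk difference) or 0.0968 (log).

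- Risk difference: 0.10/0.0484 = 2.07, power 54%.
- Log: 0.223/0.0968 = 2.31, power 63.5%.

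| Total | n per site-month | power, risk difference | power, log |
|---|---|---|---|
| 1056 | 8 | 54% | 64% |
| 1320 | 10 | 63% | 73% |
| 1390 (no dropout) | 10.53 | 66% | 75% |

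A linear time term gives the same values as monthly categories in this design.

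**Step 3: what would give 90%.** At 1320, SE = 0.0435 (log 0.0869). With 1.96 + 1.28 = 3.24, the detectable RR is 1 − 3.24 × 0.0435/0.5 = 0.72 (risk difference) or exp(−3.24 × 0.0869) = 0.75 (log). For RR 0.8, 17 (log) to 21 (risk difference) per site-month are needed, or 2244 to 2772 patients.

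**Step 4: second co-primary.** The same formula, with ICC 0.1, variance 0.03 × 0.97, a distance to the margin of 7 − 2 = 5 points and one-sided 2.5%, gives 88.3% at 9 and 91.1% at 10 per site-month with the time effect. That reproduces 1320. Without time, 5 per site-month would suffice. If the variance is averaged over the two arms, power with time at 10 per site-month is 82%.

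**Step 5: overall power at 1320, assuming independence.** Low: 0.633 × 0.82 = 0.52. High: 0.728 × 0.911 = 0.66. If the second test had 100% power, the ceiling would be 73%.

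**Cross-checks.** Simulated GLS analyses gave 54% with time and 84% without at 1056, and 63% with time at 1320. A log-link model with fixed site effects gave 50%, 83% and 59% respectively. A simulated log-link random-intercept GLMM with month effects (about 120 runs per setting) gave 58–64% at 1056 and 59–66% at 1320.

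**The case against.** The shortfall itself is hard to dispute, but several points on the other side deserve weight.

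- **How 1056 was obtained is not documented.** That time was omitted is an inference from one convention (log scale, control-rate variance). On the risk-difference scale without time, 8 per site-month gives 86%, and the no-time simulations give 82–84%. This stands. The two sizes appear to come from different models, but that cannot be proved. The shortfall does not depend on it: with a time effect, no variant tried exceeded 64% two-sided or 75% one-sided at 1056.
- **The replacement figures depend on convention.** The 73% at 1320 comes from the constant-variance log approximation. Defining the ICC on residual variance or using a log-link GEE gives 56–66%, and the small GLMM simulation gives 59–66%. This stands, and it points to lower rather than higher power.
- **50% is a cautious rate; the pre-planning data showed 61%.** At 61%, power with time is about 73–82% at 1056, 82–89% at 1320 and 84–91% at 1390 without dropout. The shortfall would then be much smaller. But the 90% is stated for 50% and 1056, where it does not hold.
- **The joint figure is soft.** It takes all 1320 patients for the second co-primary, while the Abstract restricts that endpoint to ambulatory cases. A smaller denominator would change the product. The ceiling set by the first endpoint is unaffected.
- **Recruitment could be raised.** The Recruitment section allows up to 13 per site per month. At that maximum everywhere (1716 patients), power is still only 74–83%.
- **The analysis is sound.** The model, type I error and estimate are unaffected; only the stated power and what follows from it are wrong.

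**Conclusion.** The concern holds. On the protocol's own inputs and its own analysis model, 1056 patients give about 54–64% power for hospitalization, not 90%. The planned 1320 evaluable patients give about 63–73%. Overall power above 80% is therefore unattainable at the planning rate, whatever the power of the second test; about 52–66% is realistic. The second co-primary is wrongly treated as the one that determines the sample size.

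This rests on equal recruitment of 8 or 10 per site per month, one switch per month from month 2, an exchangeable ICC of 0.15 on the total variance and large-sample Wald tests. The exact value depends on scale and ICC convention and should come from the study's own recalculation. The conclusion that 90% and 80% are not reached does not depend on those choices at the 50% rate.

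**What to change.** 1. **Sample size calculation.** Recompute the first co-primary under the model in Clinical evaluation, with the time effect, preferably by simulating that GLMM. State the software, ICC definition and variance convention. Report the power for RR 0.8 at 1320 evaluable patients (about 63–73% on the approximations above) and the RR detectable with 90% power (about 0.72–0.75). The value at a 61% admission rate can be added as a sensitivity case.
2. **Same section.** Name hospitalization as the limiting endpoint, and say that 1320 was set by the second co-primary and does not give 90% for the first.
3. **Clinical evaluation.** Replace the overall power claim with the recomputed joint power (about 52–66%), using the denominator that applies to the re-visit endpoint.
4. **Abstract.** Correct the power statement to match.
5. **Keep the time effect.** Removing it to recover power would expose the comparison to secular trends.
6. **Interpretation.** State in advance that a non-significant first co-primary is not evidence of no reduction, and rely on the confidence interval.

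The cost is a recalculation and wording changes in the protocol and SAP, with a less favourable stated power. No additional patients are required by this change.
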